### Statistical analysis

The data from the PedsQL surveys will first undergo descriptive analysis by age group surveys for children and adolescents. Numerical variables will be summarized as mean and standard deviation for variables with a normal distribution or median and interquartile range for non-normally distributed variables. Categorical variables will be summarized as absolute and relative frequencies. This descriptive approach will provide an overview of the data and support subsequent analyses (see Supplementary Table 2 for details on variables and survey items).

To evaluate the primary research question regarding the impact of the physical activity program on HRQoL, a bivariate analysis will be conducted. The analysis will compare exposure to the physical activity program (intervention vs. control group) and the PedsQL survey scores at different time points (week 0, week 11, and week 24). For numerical variables with a normal distribution, the Student's t-test for independent samples will be used. For non-normally distributed variables, the Mann–Whitney *U* test will be applied. Additionally, to evaluate within-group changes over time (e.g., baseline vs. end of study), paired tests will be conducted using either the paired Student's t-test for normally distributed variables or the Wilcoxon signed-rank test for non-normally distributed variables.

An intention-to-treat analysis will be employed to ensure the robustness of the results and account for potential non-compliance or missing data. This approach will analyze participants based on their initial group assignment (intervention or control), regardless of adherence to the program or completion of all study components (22).

Statistical significance will be set at *p*-value < 0.05. All analyses will be performed using R Studio (R Project version 4.3.2).

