### Sample size calculation

The sample size calculation for this study was conducted considering a confidence level of 95%, a power of 80%, equal variances between groups, and a 1:1 ratio between sample sizes. The difference in means to be detected was set at 4.36, based on literature identifying this value as the minimum clinically significant difference (17). The common standard deviation was calculated at 11.26, using the formula for the standard error of measurement (SEM = 15 × √1−0.85), where the Cronbach's alpha reliability coefficient is 0.85. The formula for hypothesis testing by comparing means of independent groups was applied using the Epidat 4.2 program, resulting in a required sample size of 106 participants per group. To account for an estimated 20% loss to follow-up, the sample size was increased to 133 participants per group. However, due to budgetary limitations, the final study sample will consist of a total of 90 participants (approximately 45 per group). While this is lower than the 160 participants initially estimated through power calculations, this adaptation reflects real-world constraints commonly encountered in resource-limited settings. The study is therefore best positioned as a pilot randomized controlled trial, with the aim of generating preliminary data to inform future larger-scale interventions.

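### Intention-to-treat is said to account for missing data, but analysis by assigned group supplies no missing score and the named tests use only observed scores

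*Protocol article*

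**What the plan says.** All of this is in the Protocol article.

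- **Role given to intention-to-treat** (Statistical analysis): "An intention-to-treat analysis will be employed to ensure the robustness of the results and account for potential non-compliance or missing data". The next sentence explains the approach as analysis by initial group, "regardless of adherence to the program or completion of all study components".
- **Between-group tests** (same section), applied to the PedsQL scores at weeks 0, 11 and 24: "For numerical variables with a normal distribution, the Student's t-test for independent samples will be used", and "For non-normally distributed variables, the Mann–Whitney *U* test will be applied".
- **Within-group tests** (same section): "paired tests will be conducted using either the paired Student's t-test for normally distributed variables or the Wilcoxon signed-rank test".
- **Expected loss** (Sample size calculation): "To account for an estimated 20% loss to follow-up, the sample size was increased to 133 participants per group". That section then sets the actual sample at 90, about 45 per group, for budget reasons.

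The article names no imputation, mixed model, baseline adjustment or sensitivity analysis. The Limitations section does not mention missing outcomes.

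**The concern.** Keeping each child in the assigned group answers the question of non-compliance. It does not answer the question of a survey that was never completed. A t-test or Mann–Whitney test at week 11 can use only the week-11 scores that exist, and a paired test only the children with both scores. The property claimed for the analysis therefore does not follow from the methods named.

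Two things are at stake. First, a result labelled intention-to-treat and robust to missing data would in fact rest on the children who answered. Second, an unadjusted comparison of those children can be biased if loss is related to the score and differs between arms. Unequal loss is plausible because only the intervention arm has weekly supervised sessions, held at one hospital while recruitment covers two. The article gives no evidence on it either way.

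**Working it through.** **Inputs from the article.** Difference 4.36, SD 11.26, power 80%, 1:1 allocation, p < 0.05 (two-sided assumed), planned loss 20%, actual sample 90 (Sample size calculation and Statistical analysis).

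**1. The plan's own figures.** n per group = 2 × (1.96 + 0.84)² × 11.26² / 4.36² gives 105; the t-based version gives 105.7, so 106. Allowing for loss: 106 / 0.80 = 132.5, so 133. Both stated figures are reproduced. The 20% serves only to inflate a sample that will not be recruited.

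**2. The same loss applied to the actual sample.** 0.20 × 90 = 18 children without a score; 0.80 × 45 = 36 per arm remain. Carrying the 20% over to the 90 is an assumption.

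**3. Who enters each named analysis.**

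| Analysis | Child must have |
|---|---|
| Independent t or Mann–Whitney at a visit | the score at that visit |
| Paired t or Wilcoxon | both scores of the pair |

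None of these uses the week-0 score to inform the week-11 or week-24 group comparison.

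**4. Size of a possible bias.** Bias of the observed-score comparison = d_I × gap_I − d_C × gap_C, where d is the share lost in an arm (I intervention, C control) and gap is the mean score of observed minus missing children.

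- Same rate and same gap in both arms: bias = 0.
- Loss of 25% against 15%, with a gap of 4.36 in both arms: 0.10 × 4.36 = 0.44 points; with a gap of 11.26 (one SD): 0.10 × 11.26 = 1.13 points.
- Loss in one arm only that depends on the week-0 score (odds ratio 2.7 per SD lower, assumed), and random loss in the other arm. At 19 to 20% loss the retained children in the affected arm have a mean baseline 0.165 to 0.173 SD above that of all randomised, by integrating the logistic loss model over a normal baseline. With no true effect and a baseline-to-follow-up correlation r, bias = 11.26 × r × shift:
  - r = 0.5: 11.26 × 0.5 × 0.165 = 0.93, and with 0.173, 0.97
  - r = 0.7: 11.26 × 0.7 × 0.165 = 1.30, and with 0.173, 1.36

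Simulations with 45 per arm agree: about +0.9 to +1.4 when low scorers leave the intervention arm, −0.9 to −1.35 when they leave the control arm, and about 0 when both arms lose children in the same way.

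**5. What removes that bias.** ANCOVA on the same observed children, with the week-0 score as covariate, has bias of about 0 in those simulations. It also reduces the standard error. Unadjusted, at 36 per arm: 11.26 × √(2/36) = 2.65. Adjusted, multiply by √(1 − r²): 2.30 at r = 0.5 and 1.90 at r = 0.7.

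**The case against.** **The missing-data method may be in a document not shown.** A t-test can be run on imputed scores, and a condensed article need not give the imputation method. This stands as far as it goes: one cannot say that the trial will have no protection against loss. But the article is not silent. It names intention-to-treat itself as the thing that accounts for missing data, and that sentence would be wrong whatever another document adds.

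**A reader might infer that the result will favour the programme.** The documents do not support this. It requires low scorers to leave the intervention arm more than the control arm. No differential loss is reported, and the reverse pattern gives a bias of the same size in the other direction. The Inclusion criteria require a cellphone so that surveys can be answered, so a missed session need not mean a missed survey. The Exclusion criteria remove current and recent inpatients and those with recent high-dose chemotherapy, who would be among the sickest.

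**A reader might also infer that leaving children out is what creates the simulated bias.** It is not. ANCOVA leaves out the same children and is nearly unbiased. In that scenario the fault is the lack of baseline adjustment, and the remedy works because loss was assumed to depend on baseline. Loss that depends on the unseen score would need a sensitivity analysis.

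**The study is called a pilot, and the bias is modest.** Even in the one-sided scenario it is roughly one-third to one-half of the 2.65-point standard error, with a type I error of about 6 to 8%. This limits the consequence. It does not make the statement correct, and the trial still tests effectiveness at p < 0.05.

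**Conclusion.** The point holds as a wrong statement joined to a weak choice of analysis. Intention-to-treat, as the article defines it, does not account for missing scores, and the named comparisons are available-case at each visit and unadjusted for baseline.

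The size of the possible bias rests on the assumed odds ratio, correlation and one-sided loss, none of which the article gives. Under those assumptions it is 21 to 31% of the target difference (0.93 / 4.36 to 1.36 / 4.36), in either direction. Under equal rates and mechanisms it is nil. Severity is moderate: the plan should be changed, but nothing shows that the result will be biased.

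**What to change.** - **Wording.** Say that intention-to-treat means analysis by assigned group regardless of adherence, and remove the claim that it accounts for missing data.
- **Between-group analysis.** Replace the separate tests at weeks 11 and 24 with a likelihood-based repeated-measures model containing arm, visit, their interaction and the week-0 score, using all available visits of all randomised children. A child with only one of the two later scores then still contributes. A child with neither contributes only if week 0 is modelled as an outcome rather than a covariate. ANCOVA at week 11 is a simpler alternative. Either removes bias from loss that depends on baseline and improves precision.
- **Sensitivity analysis.** Shift the missing scores in one arm, then in the other, by a fixed delta, for example up to 4.36 points. With 20% loss, the full shift moves that arm's mean by 0.20 × 4.36 = 0.87 points.
- **Reporting.** Give the number with a score by arm and visit.

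**Cost.** A few sentences and a little programming. Week-0 scores are already collected. The main analysis would rely on a missing-at-random assumption, which the sensitivity analysis probes.

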### Patient recruitment

Patients will be recruited from Hospital SOLCA Quito and Hospital Pediátrico Baca Ortiz. These two hospitals account for approximately 65% of level 3 care and treatment services in the city of Quito, with most of their patients coming from the public health sector. The remaining services are divided among other institutions: approximately 15% are provided by private healthcare facilities, while the final 20% are distributed among several public hospitals that individually account for less than 7% of level 3 care (18).

Recruitment will involve the distribution of a flyer (Figure 1) summarizing the project and inviting potential participants and their legal representatives to learn more. The flyer will also be shared digitally via mobile devices, allowing parents or guardians to review the project details at their convenience.

**Figure 1 F1:**
[figure not shown]
Promotional flier for recruitment of pediatric cancer patients for the physical activity program.

If parents or guardians express interest in learning more about the study, the medical oncologist will initiate the enrollment process by providing a detailed explanation of the project. Once the parent or guardian agrees to their child's participation, they will be required to read and sign the informed consent form and assent form. By signing these documents, parents or guardians authorize their child's medical oncologist to extract contact information and relevant diagnosis details from the medical records for inclusion in the study.

### Eligibility and randomization

This study will include participants aged 8–18 years. For study purposes, age groups will be categorized as follows:
•Children: Aged 8–12 years.•Adolescents: Aged 13–18 years (14).Participants will be randomized into one of two groups:
1.Intervention Group: Participates in a structured physical activity program.2.Control Group: Does not participate in the physical activity program.Randomization will be conducted using the REDCap randomization tool with allocation concealment ensured by restricting access to the randomization sequence (15). Medical oncologists involved in recruitment will not have access to group assignments at the time of enrollment. Additionally, the medical oncologist will be blinded for the group assignments, the social worker would know the group assignments for organization in participants for the physical activity program and surveys administered.

### Response to adverse events

Any foreseeable risk or adverse event to the participants will be classified under Gaub et Al. risks and adverse effects (16):
1.Grade 2–5: Any unfavorable and unintended sign, symptom, or disease temporarily associated with the use of a medical treatment or procedure that may or may not be related to the physical activity intervention.
•Grade 2: minimal, local, or non-invasive intervention.•Grade 3: The condition is medically significant but not immediately life-threatening; hospitalization or prolongation of hospitalization is indicated; incapacitation and limited self-care are indicated.•Grade 4: Life-threatening consequences requiring urgent intervention.•Grade 5: An adverse event that culminates in death.Grade 1: Any unintended or unfavorable sign or symptom not followed by a medical diagnosis or procedure that may or may not be related to the physical activity intervention. A single clinical or diagnostic observation occurs, and no intervention is indicated. For instance, symptoms such as shortness of breath, abdominal pain, disorientation, vomiting, bruising, headache, seizures, muscle pain, back pain, nausea, itching, and somatic reaction may be present.

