### Adverse event reporting and program oversight

Grade 1 adverse events will be reported to the corresponding medical oncologist for participant evaluation. In the event of any adverse event classified as Grade 2–5, it will be reported to the designated medical oncologists, the Cancer Committee, and the Institutional Review Board (IRB) of the Ethics Committee at Universidad San Francisco de Quito (Quito, Ecuador) for further evaluation and to determine the continuity of the program.

The social worker, together with the principal investigator, will be responsible for monitoring and reporting any potential adverse events to the medical oncologists and the IRB/Ethics Committee, should they arise during the investigation. The oversight of the data and communication among the team members will be the responsibility of the data manager to ensure proper data collection, ethical data sharing and quality control procedures for data entry.

The physical activity program will be conducted at Hospital SOLCA Quito, with support from the physical activity team, as well as a brigade of nurses and emergency room physicians who will be available to provide immediate assistance in the event of any adverse incidents during the program.

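### Seizures and disorientation are listed as Grade 1 examples, so an episode judged to need no intervention triggers no Cancer Committee review or decision on programme continuity

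*Protocol article*

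**What the plan says.** The section Response to adverse events grades events from 1 to 5. Grade 1 is "Any unintended or unfavorable sign or symptom not followed by a medical diagnosis or procedure", and the text adds: "A single clinical or diagnostic observation occurs, and no intervention is indicated". Its examples begin with "symptoms such as shortness of breath, abdominal pain, disorientation, vomiting, bruising, headache, seizures, muscle pain" and end with back pain, nausea, itching and somatic reaction. The next step up reads "Grade 2: minimal, local, or non-invasive intervention". Grade 3 covers medically significant conditions, and its wording goes on to hospitalization and incapacitation.

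The section Adverse event reporting and program oversight then sets the routes:

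- Lowest grade: "Grade 1 adverse events will be reported to the corresponding medical oncologist for participant evaluation".
- Higher grades: "In the event of any adverse event classified as Grade 2–5, it will be reported to the designated medical oncologists, the Cancer Committee" and the IRB of the Ethics Committee, "for further evaluation and to determine the continuity of the program".
- A further sentence, with no grade attached, makes the social worker and the principal investigator responsible for "reporting any potential adverse events to the medical oncologists and the IRB/Ethics Committee".

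**The concern.** Whether an event reaches Grade 2 depends on what it calls for and what follows it, not on what kind of event it is. That works for itching or nausea. It works less well for a seizure or sudden disorientation, which can end unaided and still bear on whether an exercise programme should carry on unchanged. By naming both among the Grade 1 examples, the protocol places the self-limiting episode in the tier that has no programme-level review.

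Such an event is foreseeable here. The Introduction names central nervous system tumours among the commonest childhood cancers. The inclusion criteria admit children on active treatment. The exclusion criteria remove solid tumours not yet operated on, but not operated central nervous system tumours or a history of seizures. About 45 of the 90 participants will be in the supervised exercise arm, and the Discussion lists safety among the things this pilot is meant to inform. What is at stake is whether the bodies that decide on continuity are formally asked to look at such an event.

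**Working it through.** No arithmetic beyond counting applies, and the protocol gives no figure to reproduce. The check is to apply the grading rule and then the reporting rule to one case.

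**Inputs.** The Grade 1 definition, its examples and the Grade 2 and 3 descriptions come from Response to adverse events. The reporting routes come from Adverse event reporting and program oversight.

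**Step 1: the examples.** The list is shortness of breath, abdominal pain, disorientation, vomiting, bruising, headache, seizures, muscle pain, back pain, nausea, itching and somatic reaction: 12 in all. Two are at issue, seizures and disorientation.

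**Step 2: grade the case.** Take a brief seizure that stops by itself. The clinician judges that no intervention is called for, and no diagnosis or procedure follows.

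- Grade 1 limits, "Any unintended or unfavorable sign or symptom not followed by a medical diagnosis or procedure" and "A single clinical or diagnostic observation occurs, and no intervention is indicated": both met, and seizures are a named example.
- Grade 2, "Grade 2: minimal, local, or non-invasive intervention": not met.
- Grade 3: one could argue that a seizure is medically significant, but that phrase stands beside hospitalization and incapacitation, and the explicit Grade 1 listing points the other way.

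The result is Grade 1. Self-limiting disorientation gives the same result.

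**Step 3: follow the routes.**

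| Reporting sentence | Named recipients | Cancer Committee | Continuity decision |
|---|---|---|---|
| Grade 1 | 1 (medical oncologist) | no | no |
| Grades 2–5 | 3 (oncologists, Cancer Committee, IRB) | yes | yes |
| Any potential event, ungraded | 2 (oncologists, IRB/Ethics Committee) | no | no |

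Only 1 of the 3 sentences names the Cancer Committee and a continuity decision, and the case does not meet its condition. The oncologist is told, and the ethics committee may be told through the ungraded sentence. No continuity review is triggered.

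**Step 4: test the remedy.** Deleting the two examples leaves 12 − 2 = 10. The case in step 2 would still satisfy the Grade 1 definition after that deletion, because the definition itself has not changed. A sentence about the route is needed as well.

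**The case against.** The strongest reply is that the definition governs and the list only illustrates symptoms that can occur at Grade 1. This stands, and it limits the point in several ways.

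- A reader might infer that every seizure is Grade 1. The text does not say so: a seizure that calls for intervention, or is followed by a diagnosis or procedure, no longer fits.
- A reader might take any untreated seizure to be Grade 1. That is not the test. What counts is whether intervention is called for and what follows. An episode given nothing at the time but then worked up to a diagnosis or procedure leaves Grade 1. The oncologist's evaluation may lead there.
- A reader might fear that staff will code straight from the list. That would be misapplying the scale and is no fault in the plan.
- A reader might conclude that no committee hears of the event. The ungraded sentence can be read as sending it to the IRB/Ethics Committee, which is one of the bodies in the continuity route. It does not mention the Cancer Committee or call for a continuity decision. Nor do the reporting sentences contradict each other, since all can be followed together.
- A reader might add shortness of breath to the complaint. In an exercise programme, breathlessness that needs no intervention is a natural lowest-grade event, and the existing limit is enough.

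The scale is credited to a cited source, and the article condenses a fuller protocol, so missing coding guidance is no finding. The point rests only on what is printed: which examples are named, and which grades trigger the review.

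Nurses and emergency physicians at the sessions provide immediate help, but the text gives them no role in escalation. The oncologist's Grade 1 evaluation concerns the participant, not the programme. The section Eligibility and randomization also says that the oncologist is blinded to group. If that blinding holds when the event is evaluated, judging a link to the exercise would be harder.

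**Conclusion.** The point holds in a narrow form. A seizure or disorientation episode that meets every Grade 1 limit is Grade 1 under the printed rules and does not trigger Cancer Committee review or a continuity decision. Tiering by grade is a legitimate choice; the weakness is putting these two kinds of event in the tier without programme review.

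The size is 2 of 12 examples and one reporting route. The protocol gives no rate for such events, so no expected count can be stated, and the sample size, analyses and outcomes are untouched. The conclusion assumes that the scale is applied as printed and that the full protocol, which is not shown, has no separate rule for these events. This is a cheap patient-safety improvement, not a defect that undermines the trial.

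**What to change.** 1. In Response to adverse events, delete seizures and disorientation from the Grade 1 examples. Shortness of breath may stay.
2. In Adverse event reporting and program oversight, add one sentence along these lines: *Any seizure or new disorientation, whether or not intervention is indicated, follows the Grade 2–5 route, with Cancer Committee and continuity review.*

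Both changes are needed, because the second covers the episode that would still satisfy the Grade 1 definition after the first. The cost is a small wording change and a few more committee reports. No data collection or analysis changes.
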